### Estimation of staff costs

The following steps will be followed to calculate the direct staff costs per SYI at a given site (**Figure 1**):

**Figure 1 F1:**
[figure not shown]
Pictorial representation of the steps for calculating staff costs per sick young infant for a given arm for a given trial. A – activities, F – hospital facilities, P – providers, TC – total costs, TSC – total staff costs, Tt – total time.

1 Average staff time per SYI will be calculated first at each hospital for a given staff type for each activity by multiplying the time (t = minutes per visit) and the number of visits/ SYI for the activity during the treatment period (V). The number of visits for an activity per SYI can range from one visit for assessment on admission to 21 visits for daily assessments, including vitals (generally three visits per day for 7 days of treatment). However, a given staff type, for example, one nurse may take a longer time or do more or fewer visits for an activity than another nurse at the same or another hospital. Hence, the total time (T) per SYI for each activity (A) per provider type (P) at a site under different arms and trials will be TPi = (average (ts × Vs)), where ‘i’ is for providers of the same type to get the time and visits information, and ‘s’ is for each staff member of a given provider type that is interviewed. Providers ‘i’ are nurses, medical officers/ general practitioners, paediatricians, or any other provider specified. We will take the average across providers of the same type to obtain the average time for an activity during the entire treatment episode for each arm in both RCTs.2 Staff time per provider ‘i’, per activity ‘j’ for a given hospital/facility (F) ‘k’ across all SYI getting recommended treatment will then be calculated as staff time per provider i per activity j for a given hospital k = T × N × %, where N is the number of SYI receiving activity for full days of recommended treatment (N), and % is the percentage of infants treated by a given provider for the given activity. Activity ‘j’ is described for RCT1 (**Table 1**) and RCT2 (**Table 2**) under control and interventions for staff time; ‘k’ is the hospital for which the data will be collected using the provider/hospital questionnaire.3 The average time will be aggregated for all activities for a given provider and facility by using the number of SYI receiving recommended treatment as weights for each activity.4 The total time for each staff will then be multiplied by the respective staff salaries/ minute (calculated based on annual salaries, the number of days worked in a year, and the number of hours worked in a day) at each hospital to obtain the staff costs/provider for treating all infants completing recommended treatment at a hospital.5 These staff costs will be added across the providers and then across the hospitals to obtain the total staff costs at a given site.6 These staff costs will be divided by the total number of SYI with recommended treatment under a given arm in each trial to get the staff costs/SYI for control and intervention separately for both RCTs (**Figure 1**).7 Likewise, staff costs per SYI will be calculated for each treatment arm under both RCTs for partial treatment.

### Estimation of medicines and consumables costs

The following steps will be followed to calculate the medicines and consumable costs per SYI at a given site:

For each medicine used under a given arm for a given trial, the total cost of a medicine for each SYI will be calculated by multiplying the price per vial or tablet for a medicine (P) by the quantities of medicines required per SYI (Q) for recommended treatment and the number of infants receiving the medicine (n). Average medicine quantities will differ by age and weight of the SYI [21,22], and there will be associated wastage when standard-sized injectables or tablets are used. For the hospitalised SYI, injection ampicillin is given twice daily in the first week of life, thrice daily in 2–4 weeks of life, and four times daily in four or more weeks of life. 500 mg vials will be used to draw the required doses based on the SYI’s weight and age. Assuming an average dose of 200 mg three times a day, at least two vials per day will be needed for a SYI, totalling 14 vials over seven days. With a daily requirement of 600 mg, the average wastage is 40%; at higher weights, it decreases to 25%. For gentamicin, an ampoule of 40 mg/ml or 20 mg/2 ml will be used, from which 8 mg, 16 mg, or 24 mg will be administered once daily, depending on the YI’s weight. Assuming an average requirement of 16 mg, seven ampoules of 20 mg will be needed for the control arm and two ampoules for the intervention arm in both RCT1 and RCT2. This would lead to an average wastage of 20%. For amoxicillin, 14 dispersible tablets of 250 mg will be required for seven days of treatment in RCT1 and 10 dispersible tablets for five days as an outpatient in RCT2. SYI <4 kg will require half a tablet, and those weighing >4 kg will require a full tablet. We assume, on average, 14 tablets will be dispensed for each SYI. Assuming half the SYIs are <4 kg and that, on average, only half a tablet is used from those dispensed, there would be 25% wastage.For each medicine at each hospital, the cost of each consumable will be calculated by multiplying the price per unit of the consumable (Pc) by the consumable quantities required per SYI (Qc) for recommended treatment with that medicine, and the number of infants receiving the consumable (n).The total cost of medicines will be estimated by adding the costs of all medicines at a given hospital that are needed for each arm for each RCT.Similarly, the total cost of the consumables will be estimated by adding the costs of all consumables corresponding to the medicines needed for each of the arms under the two trials at a given hospital.A few consumables are not linked to specific medicines but are related to the treatment of SYI, such as a cannula fixer, a cannula for intravenous injections, gloves, and CRP kits for protein laboratory test. These costs will also be calculated by multiplying the price per unit of the consumable (Pc) with consumable quantities required per SYI (Qc) for recommended treatment with that medicine, and the number of infants receiving the consumable (n) at the hospital.The total cost of consumables will be estimated by adding the costs of all consumables at a given hospital needed for each arm under the two trials.The total costs of medicines and consumables (estimated separately) at each site will be calculated by adding the costs at each hospital for each arm under the two trials.Average weighted medicine and consumables costs at a site will be calculated by summing the costs of all medicines and all consumables (separately) across all hospitals for each treatment arm. These total costs of medicines and consumables (estimated separately) will be divided by the number of SYI receiving recommended treatment at each hospital within a site to estimate medicine and consumable costs per SYI.For partial treatment, we will follow the same procedure (in steps 1–8) as for recommended treatment. Medicines and consumables will be calculated for three days for RCT1 and for two days after randomisation for RCT2. All medicines and consumables during the first two days of inpatient treatment will be common to both the recommended and partial treatment for RCT2.

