### Interventions and controls in the two RCTs

The RCT1 is evaluating whether experimental outpatient treatment (intervention) for YI with a single low-mortality-risk PSBI sign (*i.e.* body temperature ≥38°C, severe chest indrawing, or fast breathing of ≥60 breaths/min in 1–6-day-old infants) with injectable gentamicin (once daily) for two days and oral amoxicillin (twice daily) for seven days can be as effective as the recommended care with injectable ampicillin (2–4 times daily) and injectable gentamicin (once daily) with supportive care for seven days (control) [21]. The RCT2 is evaluating hospitalised YI with moderate-mortality-risk PSBI signs (*i.e.* body temperature <35.5°C, movement only when stimulated, or stopped feeding well), alone or in combination, or multiple low-mortality risk PSBI signs. These infants are treated similarly for the first two days with injectable ampicillin (2–4 times daily, depending on the weight of the YI) and injection of gentamicin (once daily). At 48 hours after starting treatment, if they show clinical improvement in terms of the absence of all signs of critical illness or CSI, and have a negative C-reactive protein (CRP) laboratory test, they are randomised into two groups: one is discharged on oral amoxicillin (twice daily) for five days at home (intervention), and the second group continues injectable antibiotic therapy in the hospital for five more days (control) [22].

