### Costs framework

The cost will be assessed from both the hospital and household perspectives. From the hospital perspective, medical treatment costs will be determined at each study hospital across all sites in both the intervention and control arms (**Table 1**, **Table 2**). Additionally, the household's costs will be separated into medical and non-medical costs. The hospital's indirect operational costs and households' opportunity costs in terms of wage loss will also be estimated. The costs will be weighted by infant days for each hospital, separately for the control and intervention arms, to obtain site-specific average costs for each item. To generate combined estimates, we will pool site-specific average costs across all sites to produce a single multi-country mean cost for inpatient and outpatient management, respectively.

**Table 1 T1:** Framework for provider costs under RCT1: outpatient versus inpatient management of young infants (0–59 days) with low-mortality-risk PSBI signs

Cost category	Intervention arm: outpatient treatment	Control arm: inpatient treatment
Place of treatment	Outpatient/ambulatory care	Hospital inpatient care
Antibiotic regimen	Injectable gentamicin once daily for 2 days plus oral amoxicillin twice daily for 7 days	Injectable ampicillin (2–4 times daily depending on age) plus injectable gentamicin once daily for 7 days
Staff costs	Outpatient assessment, counselling, injections preparation (canula), gentamicin administration, follow-up visits	Inpatient assessment, nursing care, injections preparation (canula) + administration, monitoring and supportive care
Medicine costs	Gentamicin and oral amoxicillin	Ampicillin and gentamicin
Consumables	Syringes, needles, cotton swabs, gloves, cannula, spirit	Syringes, needles, intravenous supplies, cotton swabs, gloves, cannula, spirit
Inpatient bed costs	Not applicable	Included for the duration of hospitalisation. Captures costs in the paediatric wards, such as costs of non- consumables, utilities, security, and laundry
Operational and indirect costs	Training, supervision, communication, administration and programme support	Training, supervision, communication, administration and programme support
Weighting approach for pooled analysis	Infant-days (number of infants treated and days each medicine or consumable is used)	Infant-days (number of infants treated and days each medicine or consumable is used)

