Coverage of sick YIs (SYI) assessed, enrolled and treated under both RCT1 and RCT2 for control and intervention.Data on two outcome variables for all SYI covered under different treatment arms. Well-trained independent outcome assessor visits all enrolled cases on days two (only for RCT1), four, eight, and 15 after the initiation of treatment to assess the study outcomes in both intervention and control arms.Average annual salaries of nurses, paediatricians, medical officers and any other staff supporting treatment. To calculate staff costs per minute, data will be collected on the average number of days in a month and the average number of hours in a day that staff work.Staff time will be considered only for activities that are linked to hospital staff and not those linked to research staff, such as outcome assessment or treatment documentation (**Table 1**, **Table 2**). The activities for the staff time will be based on a pre-defined implementation strategy [21,22].Data will be collected for SYI that receive at least 80% of the treatment (recommended treatment) and those who receive <80% of seven-day (<5.5 days) treatment (partial treatment). The latter occurs due to a treatment failure, a change in treatment, readmission, left voluntarily, or death. For the recommended treatment, we will collect costs for the seven-day treatment period following the initial assessment, across both study arms and both trials. For partial treatment, medical costs will be calculated for an average treatment period of three days in RCT1 after the initial assessment, and for two days in RCT2 in both inpatient and outpatient arms after randomisation. Costs for enrolled SYI will be weighted by the proportion of participants receiving 80% recommended treatment and those receiving partial treatment, with weights set to SYI for each group. This prevents any child randomised and enrolled from being missed. Costs due to complications, changes in treatment, and/or readmission are outside the seven-day recommended treatment window in both study arms of both trials and will not be collected.Data on staff time per visit for an activity and the number of visits undertaken for each activity during the recommended treatment period will be collected by interviewing at least 3–5 staff of each type at each hospital.The staff time for all visits during the treatment period will be weighted by the number of days an infant receives the activity and the number of YI receiving the activity (defined as weighted by infant days). For the first activity assessment on presentation at the hospital, the number of SYI will be all enrolled for a given treatment, whether partial or recommended. For all other activities, SYI who receive 80% recommended treatment will be considered to have received seven days of treatment, and those receiving partial treatment for an average of three days to calculate the costs for those enrolled.The average exchange rate used to convert all the cost estimates in local currency into USD will be for 2024, the period for which the salaries of providers, prices and household costs will be reported. It will ensure consistency, and inflation rate adjustments will not be needed for cost calculations. The recommended treatment period will be seven days for inpatient treatment in the control arm and seven days for outpatient treatment in the intervention arm for RCT1. For RCT2, the average length of inpatient treatment is 48–72 hours, prior to a negative CRP laboratory test. In RCT2, the control group after randomisation will continue receiving inpatient care for five days, while the intervention group will be discharged from the hospital on oral amoxicillin for five days to be taken at home. Both arms will share the initial hospitalisation costs during the first two days in RCT2, including CRP test costs (including staff time, kits, and laboratory costs).The data on quantities used of injection gentamicin, injection ampicillin and oral amoxicillin will be as per the recommended treatment and partial treatment per SYI for each treatment arm under each RCT.The number of SYI receiving specific medicines and consumables for each arm under both RCTs will be calculated based on the numbers receiving recommended treatment and those receiving partial treatment.Information on types and quantities of consumables required with each medicine will be collected separately for each hospital and each arm under both RCTs. The cost of medicines and consumables will be charged per size in which they are dispensed. Medicine dosage varies with the weight of the YI [21,22]. Price will be taken for full strength, and the rest will be marked as wastage. Price data will be taken from the hospital's pharmaceutical department (if available); otherwise, the market price or the WHO price will be used.Data on annual financial expenditures and admissions in the newborn intensive care units or paediatric wards where YI with PSBI are treated as inpatients at the hospital will be collected and allocated based on patient days to calculate the inpatient bed costs/ SYI treated as an inpatient. These expenditures include administration, utilities, laundry, security, data management, internet, non-consumables and other costs in the hospital inpatient ward.Hospital ambulance to transport enrolled SYI under a specific treatment arm is a cost to the hospital. It is difficult to get this information separately for each enrolled SYI under different treatment arms from the hospital data. Indirect estimation based on the average trip cost and the number of SYI using free public ambulances, estimated from household data for each treatment arm in RCT1 and RCT2, will be used.Hospital data will also be collected for operational costs, which help to strengthen the assessment, identification, and treatment of SYI with PSBI. These include training, supplies, and communication. The total costs under these three will be estimated per SYI assessed. Staff training costs include the costs of development of training material and training cost per staff per day based on the per diems, honorarium for trainers, venue and refreshment costs. Total training costs will be calculated for all staff who were used to assess and treat SYI and will be estimated per SYI assessed. Training costs for research staff for outcome assessment or data collection will not be collected or included. Price and quantities of supplies used during the assessment, such as timers, thermometers and weighing scales, will be prorated for PSBI assessed. Communication costs, include job aids or educational material, and the cost of videos developed and played at the hospitals for educating the mothers about the danger signs. Data will be collected on item quantities and prices from hospitals to assess total costs and costs per SYI assessed.

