### CEA

CE will be evaluated by estimating the ICER, defined as the difference in mean costs between the intervention and control arms divided by the difference in effectiveness between the two arms: ICER = (C_1_ − C_2_) / (E_1_ − E_2_), where C_1_ are the average costs for the intervention group; C_2_ are the average costs for the control group; E_1_ is the mean effectiveness measure for the intervention group, and E_2_ is the mean effectiveness measure for the control group. We will use societal costs – hospitals and households’ – medical costs (staff time, medicines, consumables); hospital inpatient bed cost, operational costs and households’ non-medical costs (transport, food and wage loss) for ICER calculations for all randomised SYI in both arms. We will also report ICER from only the provider/payer perspective using only medical costs for all enrolled SYI and those receiving at least 80% of the recommended seven-day treatment as a sensitivity analysis [27].

For RCT2, while the baseline costs will be presented for both pre- and post-randomisation for both study arms, the costs for ICER calculations will be compared only post-randomisation.

For each RCT, cost measures will be evaluated in both the control and intervention arms for all enrolled infants who receive either the full seven-day treatment or partial treatment. Effectiveness will be assessed in the same population based on clinical outcomes recorded on days two (for RCT1), four, eight, and 15 following treatment initiation. The ICER will be calculated for each RCT to assess whether the intervention is more cost-effective than the control.

There can be 4 case scenarios for ICER (**Figure 2**):

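### The flat 14 ampicillin vials per inpatient course come from rounding up one average regimen, which does not in general give the average number of vials across the age schedule

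*Protocol article*

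**What the plan says.** The section on estimating medicines and consumables costs each medicine as price × quantity per infant × number of infants. It says that quantities differ by age and weight, and gives the dosing schedule: "injection ampicillin is given twice daily in the first week of life, thrice daily in 2–4 weeks of life, and four times daily" from four weeks of age. For the quantity itself it then takes one average regimen, 200 mg three times a day from 500 mg vials, and states that "at least two vials per day will be needed for a SYI, totalling 14 vials over seven days". It adds that at a daily requirement of 600 mg "the average wastage is 40%; at higher weights, it decreases to 25" per cent. No other ampicillin quantity appears in the article.

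The Hospital data section sets the pricing rule: "Price will be taken for full strength, and the rest will be marked as wastage". Cost therefore follows whole vials, not milligrams.

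Table 1, under Costs framework, gives the RCT1 control regimen as "Injectable ampicillin (2–4 times daily depending on age) plus injectable gentamicin once daily for 7 days"; the RCT1 intervention arm receives no ampicillin. For RCT2 the CEA section says that "the costs for ICER calculations will be compared only post-randomisation", and after randomisation only the control arm still receives ampicillin.

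**The concern.** Rounding up to whole vials is not a linear operation. The number of vials needed at the average dose and frequency is one quantity; the average, over infants, of the number each one needs is another. The cost formula calls for the second, and the article supplies the first.

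The difference matters here because frequency changes with age and the youngest infants are in the trials. One of the three RCT1 entry signs is "fast breathing of ≥60 breaths/min in 1–6-day-old infants", so infants on the twice-daily schedule are eligible by design.

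The error would not cancel between arms. Ampicillin is a control-arm cost only, in RCT1 throughout and in the part of RCT2 that enters the ICER. A quantity that is too high makes the control arm look dearer and the intervention better value; one that is too low does the reverse.

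**Working it through.** **Inputs from the article.** Vial 500 mg; average regimen 200 mg × 3 a day; two, three or four doses a day by age (costing section). Whole units are priced (Hospital data). The Interventions section ties RCT2 frequency to weight instead; I use the costing section's age schedule.

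**Inputs assumed.** First week taken as age 0–6 days. Doses of 150 to 300 mg are examined as a range. The age and weight mix is not given.

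**Step 1: reproduce the plan.** 200 × 3 = 600 mg a day; 600/500 = 1.2, rounded up to 2 vials; 2 × 7 = 14. Wastage = 1 − 600/1000 = 40%. The 25% figure follows from 750 mg a day in two vials (for example 250 mg × 3): 1 − 750/1000. All of these reproduce. Drawing three doses from two vials means that a vial is shared between doses within a day.

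**Step 2: apply the same rule to the whole schedule.** Vials per day = dose × frequency / 500, rounded up.

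| Dose | 2 a day | 3 a day | 4 a day |
|---|---|---|---|
| 150 mg | 1 | 1 | 2 |
| 200 mg | 1 | 2 | 2 |
| 250 mg | 1 | 2 | 2 |
| 300 mg | 2 | 2 | 3 |

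At 200 to 250 mg no infant needs more than two vials a day, so 14 is the ceiling. At 300 mg four times daily the course needs 3 × 7 = 21. If every dose opened its own vial, the course would need 7 × 2, 7 × 3 and 7 × 4, that is 14, 21 and 28.

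Wastage at two, three and four doses is 20%, 40% and 20% at 200 mg, and 0%, 25% and 0% at 250 mg.

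**Step 3: first-week entrants at 200 to 250 mg, vials shared, frequency following age.**

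- RCT1 control, entry at age d = 1 to 6 days: (7 − d) × 1 + d × 2 = 7 + d, so 8 to 13 vials (mean 10.5 if entry ages are uniform) against 14.
- RCT1 three-day partial course, d = 1 to 6: 3, 3, 3, 3, 4, 5 against 3 × 2 = 6.
- RCT2 control, five post-randomisation days (ages d + 2 to d + 6), treatment started at d = 0 to 6: 5, 6, 7, 8, 9, 10, 10 against 5 × 2 = 10.

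**Step 4: illustrative effect on the RCT1 control mean.** Let a share f enter at 1–6 days on 200 to 250 mg (mean 10.5) and all others need 14. The mean is 14 − 3.5f.

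| f (assumed) | Mean vials | 14 is too high by |
|---|---|---|
| 10% | 13.65 | 2.6% |
| 30% | 12.95 | 8.1% |
| 50% | 12.25 | 14.3% |

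The excess is 3.5f vials per control infant (0.35, 1.05, 1.75), to be multiplied by the vial price, which is not given.

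**Step 5: what would offset it.** If a share g of infants needed 21 instead of 14, the mean would return to 14 when 7g = 3.5f, so g = 5%, 15% or 25% for the three values of f.

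**The case against.** The sentence about two vials a day is conditional. It starts from 200 mg three times daily, and at 600 mg a day two vials is the correct minimum, 14 the correct total and 40% the correct wastage. The article acknowledges variation by age and weight, and declares the wastage. One average regimen with stated wastage is a recognisable costing simplification, and detailed dosing is referred to the two trial protocols, which are not shown. Ampicillin is also one line beside staff, bed, operational, transport, food and wage costs, and no price is given.

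Most of this stands. A reader might infer that the article presents two vials a day as a minimum at every age; it does not. A reader might also infer that 14 cannot be the average whichever way vials are handled. That is not supported either: Step 5 shows mixes of young and heavier infants for which the shared-vial mean is exactly 14. Nor can 40% be tied to three-times-daily dosing in general, since 300 mg twice daily and 150 mg four times daily also come to 600 mg.

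What the objection does not remove is that the article fixes a quantity for a formula that needs an average of whole vials, and reaches it by rounding an average. Acknowledging that quantities vary does not turn 14 into that average.

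**Conclusion.** The point holds as a weakness of method, not as an arithmetic error. The 14 vials and the 40% wastage are correct at 600 mg a day. They are not in general the averages over a schedule of two to four doses a day when whole vials are costed.

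At 200 to 250 mg per dose with vials shared within a day, 14 is an upper limit, and it is too high for any control arm on those doses that includes first-week infants. With doses above 250 mg four times daily, or with one vial per dose, some or most infants would need more. The 3% to 14% range rests on an assumed first-week share, on 200 to 250 mg doses for those infants, on 14 vials for everyone else and on vial sharing.

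The age and weight mix and the prices are not given, so neither the net direction nor the size in money can be fixed. The effect on ICER and INB is probably small. The reason to correct it is that any error sits on one side of the comparison: control-arm cost in RCT1, and control-arm cost after randomisation in RCT2.

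**What to change.** Replace the flat 14 with whole-vial counts for each age and weight band of the dosing schedule, weighted by the enrolled mix in each control arm:

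- RCT1: seven days.
- RCT2: the inpatient course, with the five post-randomisation days shown separately for the ICER.
- Partial treatment: the same daily counts over the shorter periods.

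State whether an opened vial may supply more than one dose, and restate the wastage from the banded counts.

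The cost is a few lines in the costing spreadsheet and a count of control infants by age and weight band at entry, information already needed to dose them. Staff interviews and hospital surveys are unaffected.
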